### 2.11. Salivary Biomarkers Monitoring (Baseline, 3 and 6 Months)

Saliva samples will be taken from each patient using a cotton swab (Salivette^®^, Sarstedt, Marnay, France) according to the manufacturer’s instructions. The patients will be instructed to use the device to collect their saliva on the morning of the day of the visit before eating, drinking, or any oral hygiene procedure. Briefly, the swab should be kept in the mouth without touching it for 2–3 min until it is soaked and then replaced in its tube and returned to the department during the day with temporary storage in the refrigerator. Once received, the tube will be immediately centrifuged at 1000× *g* for 1 min and frozen at −80 °C until analysis. An immunology multiplex assay will be used to detect the level of selected cytokines and inflammatory mediators including IL-1β, TNF-α, IL-6, IL-8, IL-10 from the saliva samples using the ProcartaPlex Human Inflammation Panel (20 Plex) (eBioscience) according to manufacturer’s instructions [53].

### 2.12. Randomization et Data Management

Randomization will be performed using a randomization table generated by the software SAS (SAS Institute, Cary, NC, USA) in a balanced parallel design (1:1) using variable block sizes. This table will be implemented directly in an electronic case report form. A file describing the random procedure is confidentially classified at the Clinical Research Department (DRICI) in the University Hospital of Lille.

The individual data collected during the study will be reported on a source document and then recorded in a computer database via Clinsight^®^ software certified for data management in clinical trials according to the recommendations of the FDA (Food and Drug Administration). All data will be stored on a secured server. Before locking the database, the data will be monitored according to the coherence criteria agreed upon with the investigator. The data will be processed in accordance with the MR 001 reference methodology described by the CNIL (French data protection authority). Access to the data will be restricted to persons directly involved in the study. Data may only be modified by an investigator participating in the study or a staff member participating in the study. The data will be stored for a period of at least 15 years from the end of the research.

### 2.13. Statistical Analysis

All statistical analyses will be performed in an independent and blind way to the allocated group, using SAS software (SAS Institute, Cary, NC, USA). The level of significance will be set at 5%. The data will be evaluated using intention-to-treat analysis with the last observation carried forward. To ensure comparability between groups, the characteristics of the patients at inclusion will be described for each of the two study groups. Quantitative variables will be described by the mean and standard deviation in case of normality of the distribution, or by the median and interquartile range otherwise. The normality of the distributions will be confirmed by the Shapiro–Wilk test. The qualitative variables will be described by the numbers and percentages of each variable.

The variation of the gingival index (difference between baseline and 6-month measurement) will be estimated and compared between the two groups using a constrained longitudinal data analysis (cLDA) model as proposed by Liang and Zeger [54]. In this mixed linear model, the initial and post-treatment values will be coded as dependent variables, with a restriction on a value common to both groups at inclusion in order to control for the change between groups with respect to the baseline value and to take into account all available measures [55]. The mean change at 6 months between the groups (adjusted on baseline values) will be estimated by the time x group interaction term. In case of deviation from normality, the difference between the baseline and 6 month measures will be calculated and compared between groups using a non-parametric analysis of covariance adjusted on the baseline measure [56,57]. The variation between baseline and 3–6 months for BOP, plaque score, alpha/beta diversity index and levels of inflammatory mediators will be analyzed by the cLDA method described above for the primary outcome. A stepwise logistic regression analysis will be performed to investigate the impact of predictor variables on the clinical endpoint for treatment (e.g., BOP < 10%, GI ≤ 1). Descriptive analyses will be performed for the number of adverse effects, compliance and patient related outcomes.

The similarity of microbiota according to different clinical conditions will be analyzed using the Bray–Curtis and UniFrac distances. Taxonomic profiles will be analyzed using weighted linear discriminant analysis (LEfSe) and taxa will be used to generate correlation matrices (calculated using 4 similarity measures, namely Spearman and Pearson correlations and non-parametric Bray–Curtis and Kull–Black–Leibler distances) with the observed clinical outcomes [58].

Missing data on the primary outcome (irrespective of the reason for missing data) will be imputed under the “missing at random” (MAR) assumption using the chained equations method with 10 imputations. The variables used for the imputation model will be patient characteristics at randomization and treatment group. Quantitative variables will be imputed by the predictive mean matching method and qualitative variables by logistic regression models (binary, ordinal, or multinomial depending on the number and order of the modalities). Rubin’s rules will be used to combine the estimates obtained in each table of imputed data [59].

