#### 2.1.1. Primary Objective

Evaluation of the gingival index at 3 months: to compare the effect of twice-daily administration of probiotic lozenges during 3 months in addition to tooth brushing versus tooth brushing alone on gingival index at 3 months in adolescents undergoing treatment with fixed orthodontic appliances.

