### 2.7. Primary and Secondary Outcomes Variables

The primary outcome is the difference for gingival index at 6 months post-treatment [46,47]. Secondary outcomes include:

Difference between baseline and 3–6 months post-therapy for bleeding on probing (BOP) [48];

Mean number and percentage of participants with different BOP thresholds (e.g., BOP < 30%, BOP ≥ 30%), and gingival index thresholds (e.g., GI ≤ 1, GI ≥ 2) 3 and 6 months post therapy;

Difference between baseline and 3–6 months post-therapy for plaque score [49];

Differences between groups in occurrence of adverse events, compliance [50], and patient-reported outcomes [50];

Difference in the relative abundance of bacterial taxa in subgingival microbiota (alpha and beta diversity, Bray–Curtis distance and UniFrac).

Levels of 20 cytokines and inflammatory mediators in saliva at 3 and 6 months after therapy.

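### Section 2.13 applies both last observation carried forward and multiple imputation to the primary outcome without ranking them, and carrying values forward suits this design poorly

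*Protocol article*

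**What the plan says.** Section 2.13 makes these statements about missing data and the primary analysis:

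- A general rule: "The data will be evaluated using intention-to-treat analysis with the last observation carried forward". It is not limited to any outcome.
- A primary model: the change in gingival index from baseline to 6 months is to be "compared between the two groups using a constrained longitudinal data analysis (cLDA) model", with a common baseline mean, partly in order "to take into account all available measures".
- A fallback if normality fails: a non-parametric analysis of covariance on the change from baseline.
- A specific rule at the end of the section: missing primary-outcome data, whatever the reason, "will be imputed under the “missing at random” (MAR) assumption using the chained equations method with 10 imputations", pooled by Rubin's rules. On the content of that model: "The variables used for the imputation model will be patient characteristics at randomization and treatment group".

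Section 2.7 sets the endpoint: "The primary outcome is the difference for gingival index at 6 months post-treatment". Section 2.4 sizes the trial at 6 months and Section 2.13 models that time point. The primary objective in Section 2.1.1 reads instead "Evaluation of the gingival index at 3 months". Section 2.1.2 notes that 6 months is 3 months after lozenge intake ends.

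**The concern.** The two filling rules cannot both be carried out on the primary outcome. Section 2.6 places the clinical examination before allocation, so every randomised patient should have a baseline gingival index. Carrying forward then fills every later gap and leaves imputation nothing to do. The assumptions differ too. One rule takes the patient's value as unchanged; the other takes missing values as predictable from observed data. If the document is not settled before unblinding, the rule behind the primary p-value could be chosen after results are known.

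Carrying forward also poses a design problem. With the 6-month endpoint, only two earlier values exist:

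- **The 3-month value**, at the end of the 90-day intake. The Discussion says that the second 3 months serve to learn whether any effect remains after lozenges stop. Carrying this value forward assumes the answer.
- **The baseline value**, examined before plaque removal and before appliances are fitted (Section 2.6, Table 1). The Introduction and Discussion say that appliances raise the risk of gingivitis.

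In both cases the filled value enters the model as if it had been measured, so uncertainty is understated.

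**Working it through.** **Inputs from the document.** Difference 0.3, two-sided 5%, power 80%, attrition 10%, 58 per group (Section 2.4). No SD is given.

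**Step 1. The SD implied by the plan's own figure.** 58 less 10% leaves about 52 per arm. SD = 0.3 × √(52/2) / (1.960 + 0.842) = 0.546. Forward check: SD 0.545 needs 52 per arm, and 52/0.9 rounds up to 58. An SD near 0.54 is therefore consistent with the plan, but it is an inference. It affects only the error rates below, not the biases in steps 2 and 4.

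**Step 2. Expected 6-month difference after carrying forward.** Let d3 and d6 be the true effects at 3 and 6 months, and s3 and s0 the shares of patients whose last value is from month 3 or baseline, equal in both arms. The arms do not differ at baseline on average, so

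E = (1 − s3 − s0) × d6 + s3 × d3.

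| d3 | d6 (truth) | s3 | s0 | E | Error |
|---|---|---|---|---|---|
| −0.3 | 0 | 0.10 | 0 | −0.03 | spurious benefit |
| −0.3 | 0 | 0.05 | 0.05 | −0.015 | spurious benefit |
| −0.3 | −0.3 | 0.10 | 0 | −0.30 | none |
| −0.3 | −0.3 | 0 | 0.10 | −0.27 | dilution |
| 0 | −0.3 | 0.10 | 0 | −0.27 | dilution |

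**Step 3. Type I error in the first row.** SE = 0.54 × √(2/58) = 0.100, so the shift is 0.03/0.100 = 0.30 standard errors. P(Z > 1.96 − 0.30) + P(Z < −1.96 − 0.30) = 6.0%. At 20% lost, twice the planned attrition, the bias is 0.06 and the rate 9.2%. This is a normal approximation for an unadjusted comparison.

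**Step 4. Unequal dropout with baseline carried forward.** Assume no true effect and a mean index that rises by 0.4 from baseline in both arms. With 15% lost on test and 5% on control, the difference is 0.85 × 0.4 − 0.95 × 0.4 = −0.04. With the losses reversed it is +0.04.

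**Step 5. The three approaches side by side.** Large-sample simulation with 1,000,000 records, SD 0.54, all correlations 0.5, and all dropout after month 3. Multiple imputation uses baseline and group only. The constrained model is represented by its large-sample equivalent, which conditions on baseline, 3-month value and group.

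| Setting | Missing, control/test | Full data | Carried forward | Multiple imputation | Constrained model |
|---|---|---|---|---|---|
| d3 = −0.3, d6 = 0; dropout unrelated to index | 8.3% / 8.3% | −0.001 | −0.026 | −0.001 | −0.001 |
| d3 = −0.3, d6 = 0; dropout strongly related to 3-month index | 14.7% / 8.1% | 0.000 | −0.032 | +0.011 | 0.000 |
| d3 = d6 = −0.3; dropout strongly related to 3-month index | 14.7% / 8.1% | −0.299 | −0.307 | −0.289 | −0.299 |

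Carrying forward is biased in the first row even though dropout is unrelated to the outcome. The imputation model drifts when dropout depends on the 3-month index, because it omits that variable.

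**The case against.** The best defence is precedence. The carry-forward sentence sits among general conventions, while the imputation paragraph names the primary outcome. Read specific over general, imputation governs the 6-month gingival index and the carry-forward biases above do not reach it. This reading is plausible, but the document does not state it. It would also leave carrying forward in force for bleeding on probing, plaque, diversity and inflammatory mediators, which Section 2.13 analyses with the same constrained model and where the same design problem arises.

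A reader might infer three mutually incompatible rules. The text does not support that. The constrained model is an estimation method, it can rest on the same MAR assumption as the imputation, and it can be fitted to imputed datasets and pooled. Section 2.13 says that it takes in all available measures; it does not rule out imputation. The hard conflict is between carrying forward and multiple imputation.

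A reader might also infer that carrying forward favours the probiotic, or that it inflates type I error severely. Neither follows. Steps 2 and 4 show the direction changing with what is carried and who is lost. Larger error rates need attrition well above the planned 10%, or dropout that depends on the index in opposite directions by arm. Nothing in the documents points to such dropout in this double-blind placebo trial.

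Finally, the argument about an on-lozenge value standing in for an off-lozenge visit assumes the 6-month endpoint. If the 3-month objective of Section 2.1.1 governs, only baseline can be carried. The contradiction and the baseline problem remain.

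**Conclusion.** The point holds. Section 2.13 fixes two filling rules for the same outcome that cannot both apply, and ranks neither. Because the document states conflicting rules and is not merely silent, this is not a detail left to an analysis plan. Carrying forward is the one to remove: it presumes the persistence that the 6-month visit is meant to test, or it substitutes a value from before prophylaxis and appliances.

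The numerical effect at the planned attrition is modest: about 0.03 index points, a tenth of the target difference, with type I error of about 6.0% when a 0.3 effect at 3 months has vanished by 6 months, or a true 0.3 reduced to 0.27 when baseline is carried. These figures rest on assumed effects and dropout timing, and the error rate also on the back-solved SD. The main weakness is that the primary analysis is not uniquely defined.

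**What to change.** 1. Delete the carry-forward clause from Section 2.13 and keep the intention-to-treat statement.
2. Name one MAR-based primary analysis. The simplest is the constrained longitudinal model fitted by likelihood to all randomised patients with any gingival index measurement.
3. State the role of multiple imputation: support for the non-parametric fallback, or a sensitivity analysis.
4. Add the 3-month gingival index to the imputation model, which now lists only characteristics at randomization and treatment group.
5. Reconcile the 3-month primary objective in Section 2.1.1 with the 6-month endpoint in Sections 2.4, 2.7 and 2.13, so that the missing-data rule refers to one visit.

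A delta-adjusted sensitivity analysis for data missing not at random would be useful but is optional.

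Items 1 to 4 cost a few sentences of analysis wording and need no new patients, visits or data. They should be settled before unblinding.

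### A normality check on the trial's own data decides whether the primary analysis is cLDA or a non-parametric ANCOVA, so the primary method and effect measure are not fixed in advance

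*Protocol article*

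**What the plan says.** All of this is in section 2.13 (Statistical Analysis) of the protocol article.

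- **Default route.** GI is analysed with a linear mixed model that constrains the arms to a common baseline mean. The effect is defined: "The mean change at 6 months between the groups (adjusted on baseline values) will be estimated by the time x group interaction term". One stated reason for the model is "to take into account all available measures", which includes the 3-month visit.
- **Conditional route.** "In case of deviation from normality, the difference between the baseline and 6 month measures will be calculated and compared between groups". The method named for this step is a non-parametric ANCOVA with baseline GI as the covariate. It takes the place of the cLDA result; it is not described as a sensitivity analysis.
- **Normality.** "The normality of the distributions will be confirmed by the Shapiro–Wilk test". The sentence stands with the description of baseline characteristics, where it decides between mean with SD and median with interquartile range. The primary analysis has no test or threshold of its own.
- **Missing data.** The first paragraph says: "The data will be evaluated using intention-to-treat analysis with the last observation carried forward". The last says: "Missing data on the primary outcome (irrespective of the reason for missing data) will be imputed" under missing at random (MAR), from characteristics at randomization and treatment group, and Rubin's rules "will be used to combine the estimates obtained in each table of imputed data". Neither statement is tied to one of the two routes.

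Section 2.4 sizes the trial on a GI difference of 0.3 at 6 months (two-sided 5%, 80% power, 10% attrition, 58 per arm).

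**The concern.** A confirmatory analysis should have one method and one effect measure, set before the data are seen. Here both depend on a feature of the outcome data. Because the checked quantity is not named, two statisticians who follow the text faithfully could reach different primary analyses on the same data: one tests raw 6-month GI and switches, the other tests change scores or model residuals and does not.

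The routes are not interchangeable. cLDA estimates a difference in mean GI change, the quantity behind the figure of 0.3. No effect measure is given for the fallback, so a reader cannot tell whether the result would still be in GI units. The fallback also works only on the baseline to 6-month difference. A patient seen at 3 months but not at 6 informs a likelihood-based cLDA through the 3-month value, but not the fallback; nor does the listed imputation model use 3-month GI to recover that information.

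**Working it through.** **1. The planned sample size.** Inputs from section 2.4: difference 0.3, two-sided 5%, power 80%, attrition 10%. No SD is stated, so it is solved backwards.

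n per arm = 2 (1.960 + 0.842)² SD² / 0.3²

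- SD 0.541: 51.05, rounded up to 52
- SD 0.546: 51.997, rounded up to 52
- 52 / 0.9 = 57.8, rounded up to 58; 2 × 58 = 116

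The stated size is therefore consistent with an SD of about 0.541 to 0.546 and 52 evaluable patients per arm. The calculation is for a difference in means, which is what cLDA estimates.

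**2. How often the switch would be triggered.** The article gives no range, SD or distribution for GI. Assumptions: a 0–3 scale, scaled-beta scores, 52 per arm, no treatment effect, 2,000 simulated trials per scenario. Parametric ANCOVA stands in for cLDA. A Quade-type rank ANCOVA stands in for the fallback, whose exact form is not stated. The three Shapiro–Wilk columns give the percentage of trials rejected at 5% on pooled data (n = 104).

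| Baseline mean (SD) | 6-month mean (SD) | Correlation | Raw 6-month GI | Change | Residuals | Type I error, two-stage | Methods disagree |
|---|---|---|---|---|---|---|---|
| 1.5 (0.50) | 1.5 (0.50) | 0.5 | 8.8 | 4.2 | 5.0 | 4.7 | 1.9 |
| 1.0 (0.50) | 1.0 (0.50) | 0.5 | 67.8 | 5.4 | 32.8 | 4.6 | 2.2 |
| 0.7 (0.50) | 1.0 (0.50) | 0.5 | 67.3 | 9.4 | 37.3 | 4.2 | 2.6 |
| 1.0 (0.53) | 1.0 (0.53) | 0.3 | 76.5 | 3.8 | 55.1 | 5.2 | 2.6 |
| 0.5 (0.40) | 0.5 (0.40) | 0.5 | 100 | 41.4 | 96.2 | 4.8 | 2.6 |
| 0.3 (0.30) | 0.6 (0.53) | 0.5 | 100 | 94.2 | 98.5 | 5.6 | 3.7 |

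All entries in the last five columns are percentages. "Two-stage" means: test the change score, then use the rank method if normality is rejected and the parametric method otherwise. "Disagree" means that one method is significant at 5% and the other is not.

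Two things drive the trigger: how close GI lies to zero, and which quantity is tested. In the second row the same trial would switch 67.8% of the time on raw scores and 5.4% of the time on change scores.

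**3. Error rate.** The Monte Carlo standard error at 5% is √(0.05 × 0.95 / 2000) = 0.49 percentage points. The range of 4.2% to 5.6% is compatible with 5% throughout.

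**4. What the switch buys.** With a true difference of 0.3, 52 per arm, 6-month SD 0.45 to 0.54 and correlation 0.4, across four pairs of means, power was 84% to 92% for the parametric analysis and 84% to 93% for the rank version. The two disagreed on significance in 4% to 5% of trials. Any advantage of the rank version appears where scores lie closest to zero.

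These simulations include neither missing data nor the 3-month visit, so they do not measure the cost of dropping that visit.

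**The case against.** The strongest defence is that the rule is written in advance, that section 2.13 requires analysis blind to the allocated group, and that both routes compare baseline-adjusted 6-month change between arms. The test, the threshold and the exact non-parametric method are details that a condensed article may leave to the analysis plan. This stands in part. Blinding limits choice driven by the result, and the missing detail alone would not be a finding. But the article itself states the conditional replacement, and blinding does not fix the method or the effect measure beforehand.

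A reader might infer four stronger points that the text does not support:

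- **The fallback is a rank test with no estimate for Rubin's rules to combine.** The article says only that it is non-parametric. Some methods of that family give an adjusted mean difference with a standard error.
- **The switch is likely because GI is bounded.** No GI distribution is given. For change scores, rejection was 3.8% to 9.4% in four of the six scenarios.
- **The switch changes the missing-data assumption.** The imputation under MAR applies on either route, and likelihood-based cLDA also rests on MAR. If imputation comes first, cLDA too uses 6-month values imputed without 3-month GI. That carrying forward, all-available-data modelling and imputation are left unreconciled is a separate problem, whichever route is taken.
- **All secondary outcomes inherit the switch.** The article assigns the continuous ones to the cLDA method by name; it does not say that the fallback goes with it.

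**Conclusion.** The point holds in a limited form. The primary method is conditional on a check of the trial data whose object and threshold are unstated. The switch can take the result away from the mean difference for which the trial was sized, and the fallback makes no use of the 3-month GI.

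The frequency is undetermined: about 4% to 100% under the assumed distributions, and usually low if change scores are checked. Type I error is not materially inflated. Significance differed between the methods in 1.9% to 3.7% of trials with no effect and in 4% to 5% with a true difference of 0.3, so the choice would seldom decide significance but could decide what is reported. Power was about the same.

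These figures rest on an assumed 0–3 scale, assumed means, SDs and correlations, and stand-ins for both methods. The conclusion that the primary analysis is not fixed in advance rests on the text alone. The change is worth making because it is cheap and settles one effect measure.

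**What to change.** In section 2.13, state that cLDA is the single primary analysis of GI whatever any normality check shows, with the between-group difference in mean change as the effect measure and robust (sandwich) or bootstrap confidence intervals to cover non-normal errors. Replace the conditional sentence with one that reports the non-parametric ANCOVA as a supportive analysis.

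The cost is about two sentences and one standard-error or resampling option in the software, with no added patients or visits. The downside is a possible small loss of power against the non-parametric method if GI is very skewed.

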#### 2.1.2. Secondary Objectives

To compare the effect of adjunctive probiotics on the following parameters:Gingival index at 6 months (i.e., 3 months after cessation of the lozenges intake).Extent and severity of gingivitis (at 3 and 6 months).Plaque accumulation on dental surfaces (at 3 and 6 months).Relative abundance of bacterial taxa at the phylum level in the supra and sub gingival microbiota (at 3 and 6 months).Level of salivary biomarkers of inflammation (at 3 and 6 months).

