### 2.10. Microbiological Monitoring (Baseline, 3 and 6 Months)

Samples of supra gingival biofilm will be collected on the vestibular, occlusal, and lingual surfaces of the tooth with a sterile swab. Subgingival biofilm will be collected (4 sites per patient) on selected sites located on non-contiguous teeth (preferably 1 site per quadrants) at baseline, 3 and 6 months. after removal of the supragingival plaque. The subgingival samples will be collected using sterile paper points (Henry Schein, France) inserted into the most apical part of the sulcus for 30 s. All the samples (supra gingival dental plaque collected on tooth surface using a sterile swab, and sub gingival plaque collected using sterile paper points inserted in the sulcus) will be immediately placed in separate Eppendorf tubes and kept at −80 °C until analysis. Oral microbiota composition will be evaluated as described in a previous paper [52]. Microbiological analysis will be performed at Inserm U1241 NuMeCan (Nutrition Metabolisms and Cancer), University of Rennes. Briefly, taxonomy at the genus level will be assigned using the “Visualization and Analysis of Microbial Population Structures” (VAMPS) analysis pipeline web tool. Default parameters will be used for assignment at the genus level with the “Ribosomal Database Project” classification. Alpha rarefaction and diversity will be evaluated using the Observed Species metric (Sobs) and the Shannon–Weaver index. Beta diversity will be calculated using Bray–Curtis and UniFrac distances.

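### Beta diversity is assigned to a baseline-constrained cLDA without any per-patient value to enter it, and no workable between-arm comparison of community composition is stated

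*Protocol article*

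**What the plan says.** All references are to the protocol article.

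- **Objective (2.1.2).** The secondary objectives compare the effect of adjunctive probiotics on several parameters. One of them is: "Relative abundance of bacterial taxa at the phylum level in the supra and sub gingival microbiota (at 3 and 6 months".
- **Outcome (2.7).** The matching secondary outcome reads: "Difference in the relative abundance of bacterial taxa in subgingival microbiota (alpha and beta diversity, Bray–Curtis distance and UniFrac".
- **Definition (2.10).** "Beta diversity will be calculated using Bray–Curtis and UniFrac distances". Alpha diversity is defined separately, by observed species and the Shannon–Weaver index. Four subgingival sites per patient and supragingival swabs are sampled, and taxonomy is assigned at genus level.
- **Analysis (2.13).** After setting out the primary model, the section says that the "alpha/beta diversity index and levels of inflammatory mediators will be analyzed by the cLDA method described above for the primary outcome". In that model "the initial and post-treatment values will be coded as dependent variables, with a restriction on a value common to both groups at inclusion", and the difference in mean change "will be estimated by the time x group interaction term".
- **Other microbiota analyses (2.13).** "The similarity of microbiota according to different clinical conditions will be analyzed using the Bray–Curtis and UniFrac distances". LEfSe is applied to the taxonomic profiles with no class variable stated. Correlation matrices relate taxa to the clinical outcomes.

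**The concern.** A constrained longitudinal model describes a number that each patient has at each visit. A Bray–Curtis or UniFrac distance describes two samples at once. Unless the plan says how distances become one number per patient and visit, there is nothing to enter as the response and no baseline mean to constrain.

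This is more than detail left to a fuller document. The article names a method for the outcome, and the method does not fit the outcome as the article defines it. An analysis plan that followed the text would inherit the problem. One that departed from it would have to choose among several possible scalars or tests, perhaps after the data had been seen.

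At stake is the test of whether the probiotic alters overall community composition, which is listed as a secondary outcome.

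**Working it through.** No figure in the article bears on this point, so there is none to reproduce. The check is whether the outcome fits the model.

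**1. What cLDA needs.** Let Y(i,t) be the response of patient i at t = 0, 3 and 6 months, and g(i) the arm (0 or 1). The model sets E[Y(i,0)] = μ0 in both arms and E[Y(i,t)] = μt + δt·g(i) at t = 3 and 6. The effect is δt. Each patient must have a Y(i,0) that varies between patients, or the common-baseline constraint does no work.

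**2. What section 2.10 supplies.** For samples a and b with relative abundances p, Bray–Curtis is d(a,b) = ½ Σk |p(a,k) − p(b,k)|. UniFrac is likewise a function of two samples. Both carry two sample indices; Y(i,t) carries one patient and one visit. The article gives no rule for getting from one to the other: no ordination score, no distance to a centroid and no reference sample.

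**3. The obvious within-patient reading.** Take Y(i,t) as the distance between patient i's sample at t and the same patient's baseline sample. Then Y(i,0) = d(a,a) = 0 for every patient, with variance 0. The shared baseline mean is 0 by construction, and baseline adjustment removes nothing. The non-parametric analysis of covariance that section 2.13 keeps for non-normal data also adjusts for a baseline measure, so it meets the same obstacle.

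**4. Is the arm comparison made elsewhere?**

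| Analysis in 2.13 | Grouping stated | Arm named? |
|---|---|---|
| cLDA on alpha diversity | arm | yes, and the model fits |
| cLDA on beta diversity | arm | yes, but no response is defined |
| Bray–Curtis and UniFrac similarity | clinical condition, undefined | no |
| LEfSe | none stated | no |
| Correlation matrices | clinical outcomes | no |

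The one distance analysis that names the arms has no defined response. The one that could be run does not name the arms.

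**5. Could own-baseline distance replace cLDA on its own?** This was examined by simulation on assumed data; nothing in it comes from the trial. Assumptions: 52 patients per arm (58 × 0.9 = 52.2), 30 taxa, 5,000 reads per sample, and a log-scale shift of 0.8 in five taxa in one arm and in five different taxa of matching baseline abundance in the other. There were 200 runs, with 199 permutations in each.

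- t-test on within-patient Bray–Curtis distance: rejected in 4.5% of runs, about the nominal 5%.
- PERMANOVA by arm on the same follow-up samples: rejected in 100% of runs.

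The scenario was built so that both arms move equally far in different directions. It shows that distance travelled can miss a real difference between arms. It says nothing about how likely that is here.

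**6. Niche and rank.** Section 2.1.2 covers supra- and subgingival microbiota; section 2.7 lists subgingival only. Section 2.1.2 asks for phylum; section 2.10 assigns genus. Genus assignments can be summed to phylum, so the rank difference needs only a sentence. The niche difference is a real mismatch.

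**The case against.** The best reply is that a suitable scalar could exist. An ordination score, or a distance to a fixed reference, gives one value per patient and visit. So does the mean distance among a patient's own subgingival sites, if the four sites are sequenced separately, which the text leaves unclear. Section 2.13 speaks of an index, and section 2.10 refers to an earlier paper for the microbiota methods. This stands to the extent that a reader should not infer that cLDA can never be used. What the article supports is narrower: the response is not defined, so the model does not apply as written. The candidate scalars also measure different things. Spread among one patient's sites, for example, is not a difference in composition between arms.

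Other stronger readings are tempting and should be resisted:

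- **That the arms are never validly compared on microbiota.** Alpha diversity goes to cLDA by arm, and that is sound in form. Clinical condition and the LEfSe class are undefined, so arm may be intended; it is simply not stated.
- **That all pairwise distances would be treated as independent observations.** The article proposes no such analysis, so a count of pairs measures no stated error.
- **That the explanatory aim in the Discussion collapses.** The Discussion speaks of clinical outcomes being correlated with a bacterial shift, and the correlation matrices address that without a beta-diversity test by arm.

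**Conclusion.** The point holds for beta diversity alone. The article assigns this outcome to a model whose response it never defines, and it states no other workable comparison of community composition between the randomised arms.

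One listed secondary outcome is affected. The primary outcome, alpha diversity, bleeding on probing, plaque and salivary mediators are untouched by this point. No numerical bias can be attached to it, because the analysis as written has no definite form. The simulation shows only that the choice of replacement can decide the result in one assumed scenario.

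The conclusion rests on reading section 2.10 as the full definition of beta diversity. If the full protocol or the analysis plan defines a per-patient, per-visit scalar, the gap narrows to whether that scalar reflects a compositional difference between arms. The correction should be made before the data are analysed.

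**What to change.** - **Alpha diversity:** keep cLDA.
- **Beta diversity:** replace cLDA with a distance-based test of randomised arm, for example PERMANOVA on Bray–Curtis and on UniFrac at 3 and at 6 months. Permute whole patients between arms, account for baseline composition, and either pool a patient's sites or keep them together in the permutation. Add a check of dispersion, so that a difference in spread is not read as a difference in location.
- **Within-patient distance from baseline:** report it only as a supplement, because it ignores the direction of change.
- **Grouping in the microbiota paragraph of 2.13:** state treatment arm as the grouping for the comparative analysis, and label other clinical groupings exploratory.
- **Niche and rank:** make 2.1.2 and 2.7 agree on supra- and subgingival or subgingival only. Report abundance at phylum level by aggregating the genus assignments.

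The cost is wording in 2.7 or 2.1.2, 2.10 and 2.13. Samples, visits, sequencing and sample size do not change.
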